# Blended therapy for adolescents with chronic health conditions to increase fatigue-related self-efficacy (Booster): protocol for a single-case multiple baseline study

**DOI:** 10.1186/s13063-025-08960-1

**Published:** 2025-07-24

**Keywords:** Fatigue, Self efficacy, Early medical intervention, Experience sampling, Single-case experimental design, Mobile health, Lifestyle, Chronic disease, Adolescent

## Abstract

**Background:**

Fatigue is a common symptom in adolescents with a chronic health condition. Persistent fatigue and its impairments may be prevented by early intervention with Booster. Booster is a transdiagnostic blended care intervention that aims to increase fatigue-related self-efficacy (FSE). Through experience sampling methodology (ESM) via the Booster smartphone app, Booster helps users gain personalised insight into the relationship between their thoughts, feelings, activities, and fatigue. Based on this insight and shared-decision making, the participant and executive investigator set personal lifestyle goals, such as more exercise and fewer daytime naps. The previous version of Booster, PROfeel, has already been shown effective in treating persistent fatigue in youth. Booster’s value as an early intervention has yet to be studied. To better suit this aim and align with user preferences, the new Booster app includes features like goal attainment assistance, daily outcome tracking, and motivating game mechanics (e.g., rewards and a minigame). This protocol describes a study to examine the effect of Booster on FSE and the other study outcomes fatigue, school participation, life satisfaction, and perceived health. The secondary aim is to explore individual differences regarding (moment of) changes in outcomes during the Booster intervention.

**Methods:**

It is a single-centre study with a multiple baseline single-case experimental design (SCED). We aim to include twenty adolescents ages 12 to 18 years with a chronic health condition and fatigue. Booster’s effect on outcomes will be measured with a daily survey during Phase A (baseline) and B (intervention). The start of phase B will be randomised across cases. The effect will be assessed with the multiple baseline single-case randomisation test (SCRT) at the group level. Additionally, at the single-case level, we will explore change using permutation distancing tests (PDTs), single-case interrupted time series analysis (ITSA), and change point analyses. Also, we will assess participant characteristics associated with (long-term) improvements.

**Discussion:**

Booster uses innovative methods by combining tailored ESM-insight, mHealth and healthcare professional support. Group-level analysis, strengthened by single-case observational analyses, will evaluate the effectiveness of ESM-supported blended care as an early fatigue intervention and identify its potential working mechanisms. It lays the groundwork for implementing ESM tools in clinical practice.

**Trial registration:**

ClinicalTrials, NCT06562335. Registered on 24 July 2024, https://clinicaltrials.gov/study/NCT06562335.

**Supplementary Information:**

The online version contains supplementary material available at 10.1186/s13063-025-08960-1.

## Introduction

### Background and rationale {6a}

Over recent decades, advancements in paediatric healthcare have increased survival rates, leading to more children living with chronic conditions like autoimmune diseases or post-cancer treatment [1–3]. Growing up with a chronic health condition is challenging, as is shown by decreased social functioning [4, 5], delayed developmental milestones [6], and more mental health problems [4, 5, 7, 8]. Severe fatigue is a common and potentially disabling symptom. Prevalence ranges from 5 to 72%, depending on the condition and measurement instrument or method [9]. Despite this broad range, children with a chronic health condition consistently show more clinically relevant fatigue than their healthy peers [9]. Severe fatigue restricts participation in regular activities, lowers quality of life (QoL), and impacts psychosocial health [10–13]. The impact of fatigue and its treatment scarcity urged patients with inflammatory bowel disease (IBD) and juvenile idiopathic arthritis (JIA) to prioritise understanding and treating fatigue in their research agenda [14, 15]. Also in the oncology research field, improving the clinical management of fatigue has high priority [16].

Research indicates that severe fatigue is largely independent of disease activity, with either no [17, 18] or minimal associations found [19]. However, fatigue strongly correlates with transdiagnostic (i.e. generic) factors like support at home, physical activity, and depressive symptoms [20, 21]. The biopsychosocial model supports this, viewing fatigue as a result of the interplay of biological, psychological, and social factors [22, 23]. This complex interplay varies individually, suggesting no one-size-fits-all solution [24, 25]. Thus, a transdiagnostic approach is promising, [26, 27] in which universal mechanisms may be considered and targeted through personalised care [24, 25].

The significant burden of fatigue in children with a chronic health condition underscores the urgency for treating persistent severe fatigue. Even more, it emphasises the need for early interventions, specifically at a stage when fatigue-related impairments are still minimal or nonexistent. Early interventions could avert fatigue progression and prevent the development of these impairments. General self-efficacy is defined as the belief in one’s capabilities to influence events affecting their life [28]. It influences behaviour, resilience, and affect [28, 29]. Research shows self-efficacy predicts fatigue in children with JIA [18]. In youth with cancer [30] and survivors of childhood cancer [31], it was shown that self-efficacy influences QoL via fatigue. Additionally, a post-cancer physical activity intervention in children initially boosted self-efficacy, then reduced fatigue and improved QoL [32]. Therefore, we consider fatigue-related self-efficacy (FSE) a key target for early intervention.

A transdiagnostic tailored intervention that was successful in reducing fatigue severity in youth with severe persistent fatigue with a chronic health condition is PROfeel [33, 34]. PROfeel also boosted FSE in this group [33] and appeared most effective in youth with relatively less severe symptoms [34]. PROfeel combines an Experience Sampling Methodology (ESM)-based smartphone app with face-to-face feedback conversations. This blended care combination profits from the advantages of both on- and offline care. Patients completed a brief ESM survey multiple times a day to gain insight into the fluctuations of their fatigue and fatigue-related factors, as well as the underlying associations. Ultimately, via shared-decision making, patients formulated personal lifestyle goals to reduce fatigue severity and improve FSE and QoL. A similar approach may be useful as an early intervention strategy. To adapt PROfeel for early intervention, improvement areas were distilled from evaluations with patients, their parents, and healthcare professionals. In a participatory design process, the intervention was changed accordingly and renamed “Booster”. Booster is a transdiagnostic and tailored intervention for fatigue in children with a chronic health condition. Booster intends to increase FSE through personalised fatigue insight and subsequent lifestyle changes, supported by the Booster smartphone app and face-to-face care in consecutive intervention stages. By increasing FSE, the Booster intervention aims to prevent the progression of fatigue and its impairments.

This protocol outlines the overall research objectives of the Booster study, as well as the planned methods, analyses, and anticipated strengths and limitations. The focus of this protocol paper will be on describing the intervention design and the planned analyses at the group and single-case level. The Booster study combines phase III and phase II elements of the Medical Research Council framework for complex interventions [35]. It aims to test the efficacy of the Booster intervention in a new population (phase III) while also exploring potential mechanisms of action and user engagement (phase II). As such, this study represents an important step toward the future implementation of ESM-based tools in paediatric clinical practice.

### Objectives {7}

The primary objective of the study is to examine the effect of the Booster intervention on FSE and the other study outcomes: fatigue severity, school participation, life satisfaction, and perceived health. Study outcomes will be evaluated at the group level (research question (RQ) 1) in adolescents (12 to 18 years) with a chronic health condition in a stable phase. Participants will have experienced hindrance by fatigue for at least 3 months. We hypothesise that FSE increases first, followed after four weeks by decreased fatigue severity, and after six weeks by improved school participation, life satisfaction, and perceived health.

The secondary objective is to gain insight into individual differences regarding (moment of) significant change in outcomes during the Booster intervention. At the single-case level, we will explore which participants show change in outcomes (RQ2) and when these responders start to show change (RQ3). In addition, at group level, we will study whether baseline participant characteristics are predictive of improvements during the Booster intervention (RQ4) and whether long-term change can be observed (RQ5).

### Trial design {8}

This study employs a multiple baseline single-case experimental design (SCED). In a SCED, each case (i.e. each individual) serves as its own control, facilitated by intensive longitudinal data collection in two phases: Phase A (baseline) and Phase B (intervention) [36]. Randomisation of intervention start mitigates potential confounding of time due to external factors (*history*, e.g. transition from winter to summer*)* and internal factors (*maturation*, e.g. spontaneous recovery) [37]. This enhances internal validity [38], as does studying the effect across individuals with a multiple baseline design [38, 39]. Change relative to the randomised intervention start moments allows for causal inference within a SCED. Therefore, in this study, multiple participants start the Booster intervention at a randomised point in time to allow investigation of causal relationships between the intervention and study outcomes at the group level. Data is collected daily for 130 days (nearly nineteen weeks) with ESM via the Booster app on the participants’ phones.

ESM is also known as ecological momentary assessment (EMA). ESM is a validated structured diary method integrated into daily life [40]. It captures personal experiences and behaviours along with real-time fluctuations in well-being through repeated surveys over a period ranging from several days to weeks [41]. In the following sections, the ESM use is detailed, both the daily ESM for measuring study outcomes in the daily progress monitor and the intensive ESM for personalised insight in fatigue. Based on the Internal Validity subscale of the 15-item Risk of Bias in *N*-of-1 Trials (RoBiNT) Scale, our study design has fair methodological rigour (Suppl. Table 1) [38, 42]. Examples of factors strengthening the internal validity are the long intensive longitudinal data collection and the measurement of intervention adherence. SPIRIT reporting guidelines were followed in this protocol [43]. An overview of the study design is given in Fig. 1 (Suppl. Fig. 1 for more details).

**Fig. 1 Fig1:**
[figure not shown]
SPIRIT figure. Baseline and follow-up questionnaires for descriptives and covariates are filled out at T0 (baseline), T3, T4, and T5. T5 is one year after the Insight Conversation and the end of study participation. Abbreviation: FSE is fatigue-related self-efficacy

## Methods: participants, interventions, and outcomes

### Study setting {9}

Patients will be recruited from the Wilhelmina Children’s Hospital, University Medical Centre (UMC). We aim to include twenty participants. All participants have a chronic health condition (including but not limited to IBD or JIA) or a history of a life-threatening health condition (i.e. childhood cancer). Patients with a history of childhood cancer will be referred from the Prinses Maxima Centre for paediatric oncology to the specialist fatigue clinic at the Wilhelmina Children’s Hospital.

### Eligibility criteria {10}

Booster is intended for a heterogenous group of participants. Participants are eligible if they are at least 12 years and no older than 18 years at baseline; feel hindered by fatigue (≥ three months [44] with a paediatric short fatigue questionnaire (pSFQ) score ≥ 15 [45]); and are diagnosed with a chronic health condition or have been treated for childhood cancer. Participants will be excluded when another treatment for their fatigue than Booster is indicated or the Booster intervention is not feasible. The exclusion criteria concerning another indicated treatment are: a somatic or psychiatric diagnosis that fully explains the fatigue; a chronic health condition that has been unstable in the past three months (e.g. change in medication or cancer relapse); and significant functional limitations due to fatigue (e.g. school absenteeism > 50%). The exclusion criteria concerning feasibility are as follows: a cognitive impairment with an IQ < 70 as estimated by the treating physician; no possession of a smartphone with internet access; or unable to speak, read, understand or write Dutch.

As part of usual care, potential participants will undergo a standardised somatic and psychiatric fatigue analysis. Other exclusion criteria will be checked by the study team prior to enrolment.

#### Who will take informed consent? {26a}

Potential participants will receive oral and written information from the executive investigator.

#### Additional consent provisions for collection and use of participant data and biological specimens {26b}

Not applicable.

## Interventions

### Explanation for the choice of comparators {6b}

See section “Trial design”.

### Intervention description {11a}

#### Development

From September 2022 to March 2023, PROfeel was evaluated. This led to the development of a new intervention suited for early intervention (Suppl. Table 2a, b). In the iterative design process, based on Design Thinking [46], patients and healthcare professionals participated throughout (Suppl. Table 2c). The process started with interviews with former PROfeel users (i.e. (parents of) patients and healthcare professionals), followed by defining the development direction and ideation. Then, patients tested and provided feedback on consecutive app prototypes. An interdisciplinary team of game designers, medical doctors, and psychologists made design decisions. This resulted in the current intervention, renamed “Booster”. The new Booster app incorporates user preferences with features like a goal attainment module and motivating game mechanics as incentives (Suppl. Table 2d, Suppl. Figs. 2–5). The following sections describe the Booster intervention in detail.

#### Booster intervention

Booster is a patient-tailored intervention that aims to prevent the progression of fatigue and its impairments by increasing FSE. It blends on- and offline face-to-face contact with the executive investigator (hereafter: investigator), and mobile health (mHealth) support via the personalised Booster app (Suppl. Table 2d for an overview of app functionalities). Booster shifts the participant’s focus from fatigue to a modifiable area of daily life, further referred to as "lifestyle”. This shift is intended via increased insight into fatigue and related lifestyle factors through intensive ESM, followed by personalised goal-setting and -attainment (Suppl. Table 2b for Booster’s logic model). Booster comprises five stages: the Start Conversation, the Measurement Period, the Insight Conversation, the Experiment Period, and the Evaluation Conversation (Fig. 1, Suppl. Table 3), detailed in the following section. The daily progress monitor starts ten to eighteen days (depending on randomisation) before the Start Conversation. The participant will fill out this monitor via the Booster app throughout the intervention (see section “Plans for assessment and collection of outcomes”, Fig. 1 and Suppl. Fig. 1 and Suppl. Table 3).

##### Stage 1: Start Conversation

In a face-to-face meeting, the investigator explains the aim and the method of the Booster intervention to the participant, followed by information on the biopsychosocial model of fatigue (Suppl. Table 4 for an example biopsychosocial model). The participant and investigator discuss the participant’s attributes on fatigue-associated factors within the three domains. They focus on hypothesised inciting (e.g. disease flare) and sustaining factors (e.g. school pressure). This is the prelude to the personalisation of the ESM-items and -notification schedule by the participant in the Booster app. The participant is instructed to respond to ≥ 70% of the intensive ESM-surveys to provide sufficient measurement points to construct the Booster report.

**Generic and personalised ESM-items for personalised insight** The intensive ESM-survey has generic and personalised items. Item domains are based on potentially fatigue-sustaining biological (e.g. sleep, physical activity), psychological (e.g. cognitions, feelings) and social (e.g. location and company of others) factors [22, 24]. Examples of generic items are as follows: “In the last 3 h, I felt fatigued” and “In the last 3 h, I was physically active”. For personalised items, the participant can choose the exact phrasing from a list or create their own phrasing (e.g. for positive affect, options such as “happy” or “enthusiastic” are available, Suppl. Table 5 for all ESM-items for personalised insight). Besides, the participant can add extra items, for example on specific physical symptoms [33, 34]. Most items are answered on a visual analogue scale (VAS) ranging from 0 (“not at all”) to 100 (“very much”). Likert options are shown on the answering scale (e.g. “a bit” for scores 21 to 40) instead of the exact score selected (e.g. 31). The rating from the previous measurement time will be visualised during the current measurement with the label “last”. This implicit reference point decreases measurement error and improves user experience [47]. For categorical items like location, the participant chooses between options or fills in the exact answer in the “other” option. This personalised option will be automatically added at the next measurement time (Fig. 2).

**Fig. 2 Fig2:**
[figure not shown]
Examples of ESM-items for personalised insight in the Booster app. The survey is called “Check-up” All questions refer to the last three hours. **A** VAS-scale question, ranging from “Not at all” to “Very much”. The label “last” shows the response at the previous measurement time. The slider shows Likert scale-like options (“Quite a lot”). **B** Multiple choice question, displaying the standard (first six) options along with a personal option. The “someone else” options filled in previously will be shown in subsequent measurement times, with a maximum of two additional options

##### Stage 2: Measurement Period

For four weeks, the participant receives the intensive personalised ESM-survey five times daily via the Booster app with an approximate three-hour interval. The first survey of the day arrives at 9 AM, 10 AM, or 11 AM, based on the participant’s schedule choice during the Start Conversation. The exact timing of notification is randomly assigned within 30 min of the scheduled times. In case of non-response, reminders are sent after 20 and 60 min. After 90 min without response, the survey closes and is marked as missing. Completing the intensive ESM-survey costs less than one minute.

From PROfeel research [34], we know that a compliance of at least 35% (i.e. 49 completed surveys) is required to derive a Booster Report. Yet, the reliability of the output increases as the number of completed surveys does. Therefore, in line with previous research [48], we aim for at least 70% compliance. Extension of the Measurement Period will be offered to the participant in case of < 70% compliance. If the participant does not want to extend the Measurement Period, the researcher must discuss the content of the report with more caution because of the lower reliability (see section “Stage 3: Insight Conversation”).

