##### Stage 3: Insight Conversation

After the four-week Measurement Period, the participant has a face-to-face conversation with the investigator. The Booster report, based on the intensive ESM-surveys, is discussed and lifestyle goals are set using shared-decision making.

**Creating the Booster reportCreating the Booster report** A statistician, blinded to the participant, uses the intensive ESM surveys to compute an individual statistician report. This contains a summary of fatigue-sustaining factors and their dynamic networks. The summary includes fluctuations across the whole assessment period, averages for assessment hour and day of the week, differences for categorical factors, and day-to-day associations between paired ESM items across the Measurement Period. The dynamic networks (vector autoregression lag 1) are produced using Residual Dynamic Structural Equation Modelling. This method corrects for moving weekly average trends, weekend, and time of day and has been described more elaborately elsewhere [24, 48–50]. From all the generated output, the statistician and investigator independently select the most relevant summary figures and dynamic networks to be included in the Booster report (Fig. 3). Relevance is based on statistical significance, magnitude of standardised estimates, and assumed usefulness for the participant. Possible differences between selections are settled via discussion between the statistician and investigator.

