### Sample size {14}

The power to detect an intervention effect with a multiple baseline design (RQ1) depends on the autocorrelation of consecutive daily progress monitor measurements, the start moment range, the number of repeated measurements, the intervention effect, and the number of cases [52]. In the earlier PROfeel study [48], the median autocorrelation of weekly measurements was 0.17 for FSE, 0.30 for fatigue severity, and 0.09 for QoL. Median autocorrelation of the five times daily ESM item on fatigue severity was 0.37 [48]. We expect the daily measurements in this study to show a higher autocorrelation than weekly measurements, but lower than a five times daily item. Thus, we assumed the autocorrelation in our study to be 0.30 across outcomes. The start moment range is nine, as the Booster intervention is randomised to start (T1) ten to eighteen days after the start of the daily progress monitor (T0). With 100% compliance, the number of repeated measurements is 130. With the abovementioned assumptions and inclusion of twenty cases, with up to 30% of daily measurements missing, the multiple baseline single-case randomisation test (SCRT) can detect medium to large intervention effects of ≥ 0.7 with a power of ≥ 0.80 at the group level (RQ1, Table 1). However, we anticipate small intervention effects since Booster is an early intervention, not treatment. The SCRT, used in SCED, has limited power to detect such small intervention effects [37, 52, 53]. In contrast, the permutation distancing test (PTD), developed for testing differences in means in single-case observational designs (SCODs), exhibits higher statistical power [53]. It is important to note that SCOD cannot establish causality. With the abovementioned assumptions, with up to 40% of daily measurements missing, the study is well powered to observe changes in outcomes for effect sizes as small as 0.3 at the single-case observational level (RQ2, Table 1).

**Table 1 Tab1:** Power for detecting intervention effects at the group and single-case level

Factors influencing power	Study design	
Autocorrelation (%)	30	
Repeated measurements (*n*)	130	
Power (%)	≥ 80	
Cases (*n*)	20 (group level)	1 (single-case)
Test	Multiple baseline SCRT	PDT
Start moment range (*n*)	9	NA
Maximum percentage missing data to retain sufficient power (%)	30	40
Minimum detectable effect size	0.7 (medium to large)	0.3 (small)

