### Data collection and management

#### Plans for assessment and collection of outcomes {18a}

Study outcomes will be assessed using the daily progress monitor, a repeated survey. The Booster app sends the daily progress monitor at a random time within the hour before bedtime. Participants determine the exact timing of completing the monitor, provided it is within three hours of receiving the notification. Responses not submitted within this three-hour window are considered missing. For each item, participants are asked to reflect on their day. Item order is randomised to minimise method bias [56]. The daily monitoring period starts ten to eighteen days before the Start Conversation and continues for 130 days, ending twelve weeks into the Experiment Period.

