## Statistical methods

### Statistical methods for primary and secondary outcomes {20a}

#### RQ1: What is the effect of the Booster intervention on the study outcomes at the group level?

We will study change in mean level of outcomes (level change) after outcome-specific lags (Suppl. Figure 1). We hypothesise that FSE, Booster’s main target, will improve immediately after the Insight Conversation. Improvements in fatigue and participation are expected four weeks later, with life satisfaction and perceived health improving at six weeks post-Insight Conversation. After visual inspection of the data, the multiple baseline SCRT will determine the presence of significant medium to large Booster intervention effects at the group level. The null hypothesis is that observed outcomes are independent of intervention phase. The randomisation of intervention start is a precondition for conducting the SCRT. It tests significance by comparing the observed test statistic (mean level change) to the test statistic distribution of all other possible intervention start points. This controls for time-related confounding [60, 61]. The SCRT outcomes will show if the Booster intervention is effective at the group level.

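### RQ1 does not say how the randomisation test splits participants whose Measurement Period is extended; a split on the unextended schedule loses power, and the actual Insight Conversation date against the unextended reference set inflates type I error

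*Protocol article*

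**What the plan says.** **What is randomised.** Sample size {14}: "The start moment range is nine, as the Booster intervention is randomised to start (T1) ten to eighteen days" after the daily progress monitor begins. Nothing else in the schedule is randomised.

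**Where the effect is looked for.** RQ1 expects that FSE "will improve immediately after the Insight Conversation", with the other outcomes following four or six weeks later. The Sample size section gives every outcome a Phase A of about six weeks, so the phase split is not at T1.

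**How T2 follows from T1.** Stage 2 sets the length: "For four weeks, the participant receives the intensive personalised ESM-survey five times daily". Stage 3 places T2 at its end: "After the four-week Measurement Period, the participant has a face-to-face conversation with the investigator".

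**What can move T2.** Stage 2 also says: "Extension of the Measurement Period will be offered to the participant in case of < 70% compliance". It gives no length, and the participant may decline.

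**The test.** RQ1 works by "comparing the observed test statistic (mean level change) to the test statistic distribution of all other possible intervention start points", calls randomisation of the start a precondition, and defines lags by outcome.

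**End of monitoring.** Section {18a} says the monitor "continues for 130 days, ending twelve weeks into the Experiment Period". Participant timeline {13} instead runs it until the Evaluation Conversation (T3).

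**The concern.** A randomisation test is exact when the observed split is one of the splits that the randomisation could have produced, and when the reference set is built by the same rule. Here the split is at T2 or later, and T2 inherits its randomisation from T1 through a constant 28 days. Once T2 can also move with compliance after randomisation, that link is broken for extended participants.

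Read with lags fixed per outcome and counted from the randomised start, the test splits an extended participant before the actual T2. Some days before the Insight Conversation are then counted as Phase B. Read with the actual T2 as the split, but with the nine scheduled starts as the reference set, the observed split can lie outside the set it is compared with. The SCRT is the study's only causal test, and the protocol itself says its power is limited to medium to large effects.

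**Working it through.** **Inputs from the protocol.** 20 cases; T1 uniform on days 10-18 (nine starts); Measurement Period of 28 days; 130 daily measurements; autocorrelation 0.30; up to 30% missing; effect 0.7 with power of at least 0.80 (Sample size {14}, Table 1).

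**Assumptions, not in the protocol.** Alpha 0.05, one-sided; measurements missing at random; the share who extend (10%, 25%, 50%) and the length (7 or 14 days). As a gauge of length: 70% of 28 × 5 = 140 surveys is 98. At compliance c, reaching 98 at an unchanged rate takes (98 − 140c)/(5c) more days: about 5 at 60%, 11 at 50% and 28 at 35%. The protocol does not say that extension runs until 98 surveys are reached.

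**Step 1: position of the split.** Scheduled T2 = T1 + 28 = day 38 to 46. With an extension of e days, the actual T2 = T1 + 28 + e. It falls outside days 38-46 for e of the nine starts when e is 8 or less (7 days: 7 of 9) and for all nine when e is 9 or more.

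**Step 2: the plan's own figure.** Series were AR(1) with unit SD and a level shift at T2. The statistic was the mean over cases of (mean of B − mean of A), with 2,000 simulated trials and 299 re-randomisations each. Without extensions, power is 0.82 at effect 0.7 and 0.71 at 0.6, which reproduces the stated minimum of 0.7. Two-sided power at 0.7 is 0.70. A split at T1 gives 0.71 one-sided.

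**Step 3: add extensions and compare three analyses.**

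| Extended | Scheduled split: power | Actual T2 against days 38-46: type I error | Own T1-T2 interval carried through: power / type I error |
|---|---|---|---|
| none | 0.82 | about 0.05 | 0.82 / about 0.05 |
| 10%, 7 days | 0.74 | 0.07 | 0.82 / 0.04 |
| 25%, 7 days | 0.59 | 0.10 | 0.82 / 0.05 |
| 25%, 14 days | 0.60 | 0.16 | 0.82 / 0.06 |
| 50%, 7 days | 0.34 | 0.14 | 0.83 / 0.05 |
| 50%, 14 days | 0.35 | 0.21 | 0.82 / 0.05 |

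Repeat runs differ by about 0.02 at most: 0.72-0.74 for power in the 10% row, and 0.20-0.22 for type I error in the last row. Under the scheduled split, type I error stays at about 0.05 throughout.

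The type I errors in the table assume no time trend. In smaller runs (600 trials, 14-day extensions), the actual-T2 analysis against days 38-46 reached 0.30 (25% extended) and 0.43 (50%) with an accelerating trend of 1 SD. With a trend that levels off early it fell to about 0.02-0.03.

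**Step 4: length of monitoring.** T0-T1 plus Measurement Period plus Experiment Period is 10 + 28 + 84 = 122 days at the shortest and 18 + 28 + 84 = 130 at the longest. The slack under 130 days is therefore 18 − T1, or 0 to 8 days. Any extension beyond that slack puts twelve weeks after T2 past day 130.

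**The case against.** The strongest reply is that RQ1 commits to neither harmful version. The randomised start is T1, so permuting T1 while each participant's own T1-T2 interval is held fixed fits the wording about all other possible start points, and an SAP might say so. This is right in part: a reader might infer that the test must lose either power or its error rate, and the third analysis in the table shows that it need not. What remains is that the stated ingredients (lags per outcome, nine start points) do not lead to that analysis for an extended participant, while Stage 2 makes the split depend on compliance.

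Three further limits stand:

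- **The scheduled split is a valid test.** A reader might infer that it is biased towards a false positive. The simulations show a loss of power only.
- **The days before an extended T2 are not simply untreated.** The Start Conversation and Measurement Period are stages of the intervention, and the Discussion allows that change may begin then. The simulated power loss assumes that the whole effect arrives at T2, as RQ1 hypothesises for FSE.
- **Loss of late Phase B data is not established.** A reader might infer it from the 130-day figure. But Participant timeline {13} runs the monitor until T3, an event that follows the actual T2. The documents give conflicting end rules and do not state a cut-off that removes data.

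Extensions may also be few. They are optional, and reminders and rewards support compliance. With none, the primary test is unaffected.

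**Conclusion.** The point holds as a gap between the extension rule and the primary test. If the split follows the unextended schedule, power at effect 0.7 falls from 0.82 to about 0.72-0.74 with 10% extended by 7 days, about 0.60 with 25% and about 0.34 with 50%. If the actual T2 is tested against days 38-46, type I error is about 0.07 to 0.22 in the same scenarios without trend. Even two extended participants out of 20 take the scheduled-split power below the stated 0.80.

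These sizes rest on assumed extension shares and lengths, a one-sided 5% test and an effect that starts at T2. The choice of split should be fixed before the outcome data are analysed, because a choice made afterwards would depend on the data.

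The 130-day figure is a separate, smaller inconsistency. It agrees with twelve weeks of Experiment Period only for a day-18 start without extension. If it were applied as a hard stop, it would shorten Phase B for participants whose extension exceeds their slack of 0 to 8 days.

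**What to change.** In RQ1, state that the split is each participant's actual T2 plus the outcome lag. State also that the permutation redraws only the randomised 10-18 days and holds each participant's observed T1-T2 interval fixed, so that the observed split always belongs to the reference set. Name the assumption this needs: extension length does not depend on the assigned start day. Report the number and length of extensions, and add a sensitivity analysis, for example without the extended participants.

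Separately, reconcile the fixed 130 days in Trial design {8}, Sample size {14} and section {18a} with the two event-based end points: twelve weeks into the Experiment Period ({18a}) and the Evaluation Conversation ({13}).

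The cost is a few sentences of analysis text, a small change to the permutation code and one consistent definition of when monitoring ends. In the simulations the recommended analysis costs no power against the plan's own figure.
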